### Exclusion criteria

An overview of the maternal and neonatal exclusion criteria is provided in Table 1. The criteria are predominantly clinical variables considered to influence the composition of the gut microbiota.

### Sample size calculation

A formal power analysis could not be performed as there are currently no relevant data in the literature on the 16S rRNA gene-sequencing technique. For this study, we aim to include 60 children: 20 born vaginally and 40 born by CS (20 from mothers receiving antibiotics before CS and 20 after clamping of the umbilical cord).

### Study materials and samples

At an outpatient clinic prior to their scheduled CS or vaginal delivery, all women will be asked to take a vaginal swab and a rectal swab. The swabs will be stored at − 20 °C directly after sampling.

To determine to what extent neonates from group A have been exposed to cefuroxime, we will collect umbilical cord blood from these infants after clamping of the cord and delivery of the placenta. The blood will be collected in an ethylene-diamine-tetra-acetic acid (EDTA) tube. Directly after collection, the samples will be stored on ice before further handling.

Parents are asked to collect faecal samples from the neonate (approximately 2 g or more), in sterile stool containers (10 mL, Frickenhausen, Germany) on days 1, 7 and 28 and at age 2 years (at home). These samples are stored at − 20 °C (at home in a domestic freezer), within 1 hour of collection.

An oral swab will be taken from the neonate directly after birth to evaluate the presence of maternal microorganisms (vaginal and faecal). The swabs are stored at − 20 °C within 1 hour following collection.

When the child reaches the age of 2 years, a questionnaire will be sent to the parents focusing on the child’s health status. Items include information on allergies, use of medication, hospital admissions, number of visits to the general practitioner and the use of antibiotics between birth and collection of the follow-up sample.

Depending on the results of the analyses, we will schedule a follow-up of the children later in early childhood.

### Data management and monitoring

All study participants will receive a study identification number. Electronic data will be kept in a secure password-protected database. The data collected will be stored at the research unit in the study centre. All data will be securely stored, backed up and retained for 15 years. Additional consent from both parents will be obtained to store and use this data in future studies. Only relevant members of the research team will have access to the data. A data safety monitoring committee is not required according to the guidelines proposed by Ellenburg et al. [22]*.* The study will be independently monitored at study close-out. No interim analyses will be performed.

### DNA extraction and microbiota analysis using 16S rRNA gene sequencing

Stool samples from infants will be collected, as reported above, on days 1, 7 and 28 and at 2 years old. DNA will be extracted, as documented previously by Daniels et al. [23]. From the purified faecal DNA, extracts of the V3-V4 hypervariable regions of the bacterial 16S rRNA gene will be amplified, using universal primers S-D-Bact-0341-b-S-17 (forward 5′-CCTACGGGNGGCWGCAG-3′) and S-D-Bact-0785-a-A-21 (reverse 5′-GACTACHVGGGTATCTAATCC-3′) [24]. Sequencing will be performed by LifeSequencing SL (Valencia, Spain) on an Illumina MiSeq instrument (San Diego, California, USA).

### Statistical analysis

Baseline characteristics will be summarised for all subjects by treatment regimen and compared between groups.

The primary outcome will be differences in the microbiota between the two groups of infants born by CS on day 28. An adaptation of QIIME v1.9.0 [25] will be used to analyse the sequenced data. Briefly, sequences will be clustered into operational taxonomic units based on 97% sequence identity as a proxy for bacterial species using VSEARCH v2.03 against the RDP gold database and by excluding chimeric sequences [26]. Taxonomic assignment will be performed using the RDP classifier [26] against the SILVA119 database [27]. The species diversity (α-diversity) of faecal and salivary samples will be calculated using Faith’s phylogenetic diversity [28] and the Shannon index for diversity [29] and by applying a correction for differences in sequencing depths by rarefaction. Furthermore, absolute and relative abundances as well as unsupervised and supervised classification methods will be used to evaluate the influence of timing of intrapartum cefuroxime administration on the composition of the microbiota.

Clinical outcomes at the 2-year follow-up will be compared using Student’s *t*-test or a Mann–Whitney *U* test for continuous variables depending on whether the variables are distributed normally. A χ^2^ test or Fisher’s exact test will be used to compare normal and non-normal dichotomous variables, respectively. Differences between groups will be presented for continuous outcomes as differences in means or differences in medians (for normal or non-normal distributions, respectively) along with a 95% confidence interval. For dichotomous outcomes, the relative risk and number needed to treat will be determined along with a 95% confidence interval. All comparisons will be made between the randomised exposed (group A) and the unexposed (group B) infants born by CS. Furthermore, all analyses will compare infants from both CS groups together (groups A and B) with children born vaginally (group C) and lastly infants born vaginally will be compared with the two CS groups separately. Differences between study groups will be considered significant if *p* < 0.05.

If differences exist between the groups in terms of feeding strategies or other baseline characteristics, we will adjust for this in the statistical analysis. Since nutrition affects the microbiota and antibiotics might be present in a limited concentration in breast milk, we will perform the same analysis for infants fed only by formula and for infants breastfed only and adjust for this factor. Furthermore, the concentration of cefuroxime in the umbilical cord blood will be valuable in interpreting the influence of the these factors.

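### For sparse counts among the secondary 2-year outcomes, Mann-Whitney is paired with a difference in medians that can be zero beside a significant test

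*Protocol article*

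**What the plan says.** The rule is in the Statistical analysis section of the protocol article. It opens "Clinical outcomes at the 2-year follow-up will be compared using" and goes on to name Student's t-test or Mann-Whitney for continuous variables, "depending on whether the variables are distributed normally". The effect is then to be presented as "differences in means or differences in medians (for normal or non-normal distributions, respectively) along with a 95% confidence interval". Dichotomous outcomes have their own route: chi-squared or Fisher's exact test, with relative risk and number needed to treat. No third route is given for counts, so a count that is not dichotomised falls under the continuous rule.

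The items come from the parent questionnaire described under Study materials and samples: "Items include information on allergies, use of medication, hospital admissions, number of visits to the general practitioner", together with antibiotic use since birth. Only the visits are explicitly a number. The scale on which admissions and antibiotic use are recorded is not stated.

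The randomised comparison has 20 children per arm (Sample size calculation: "20 from mothers receiving antibiotics before CS and 20 after clamping of the umbilical cord"). The same rule also serves the comparisons with the vaginally born group.

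**The concern.** The test and the estimate on the non-normal branch answer different questions. Mann-Whitney asks whether a child in one arm tends to have a higher value than a child in the other. A difference in medians looks only at the middle of each distribution. When more than half of the children in both arms have no events, both medians are zero, however many events the remaining children have.

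Health state at 2 years is a secondary objective, and the article has no power calculation. Readers will therefore lean on estimates and intervals more than on p-values. An estimate held at zero by construction could hide a real difference in a sparse outcome, or leave a significant p-value with no interpretable size.

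A second, smaller issue is that the observed distribution decides whether a mean or a median difference is reported, so the quantity being estimated is not known in advance.

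**Working it through.** The plan gives no event rates, so there is no stated figure to reproduce. All rates below are assumptions.

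**Inputs from the article.** 20 v 20 children; significance at p < 0.05 (two-sided assumed); Mann-Whitney with a difference in medians if non-normal.

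**1. Can it happen? A constructed example, 20 per arm.**
- Arm 1: 11 zeros, 3 ones, 4 twos, 2 threes. Events = 3 + 8 + 6 = 17, mean 17/20 = 0.85, median 0.
- Arm 2: 18 zeros, 2 ones. Events = 2, mean 2/20 = 0.10, median 0.
- Shapiro-Wilk rejects normality in both arms (p < 0.001), so the plan selects Mann-Whitney: p = 0.009 (permutation p = 0.008).
- Reported estimate: difference in medians 0 − 0 = 0, although the ratio of means is 0.85/0.10 = 8.5.

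**2. How often, for a sparse count? Poisson 0.15 v 0.45.** With 20 children the median is 0 only if at least 11 have no event.
- P(no event) = exp(−0.15) = 0.861 and exp(−0.45) = 0.638.
- P(at least 11 of 20 zeros) = 0.9999 and 0.852 (binomial).
- P(both medians 0) = 0.9999 × 0.852 = 0.85. Simulation of 4,000 trials gives 86%.
- In one such run, 32.4% of trials were significant and 20.5% were significant with a median difference of 0: 20.5/32.4 = 63%. A second run gave 67%, hence about two thirds.

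**3. How this depends on the rate.**

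| Assumed means | Share of significant Mann-Whitney results with median difference 0 |
|---|---|
| 0.1 v 0.6, 0.1 v 0.8, 0.2 v 0.8 (negative binomial) | 52% to 71% |
| 0.15 v 0.45 (Poisson) | about two thirds |
| 0.3 v 0.6 (Poisson) | 21% |
| 0.3 v 1.0 (negative binomial) | 14% |
| 2 v 4 (negative binomial) | below 0.1% |
| 4 v 6 (Poisson or negative binomial) | 0.1% or less |

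**4. The switch, for frequent counts (4 v 6).** Taking Shapiro-Wilk at 0.05 as the check, both arms pass in 64% of trials (Poisson), 38% (negative binomial, size 4) or 14% (size 2). The t-test and Mann-Whitney disagree on significance in 6% to 9%.

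**5. Type I error of the two-stage rule.** With equal counts in both arms it was 5.1% to 5.9% over three assumed scenarios, close to nominal.

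**6. Would the Hodges-Lehmann shift repair it?** In the example there are 20 × 20 = 400 pairs.
- Arm 1 higher: 9 × 18 + 6 × 2 = 174.
- Tied: 11 × 18 + 3 × 2 = 204.
- Arm 1 lower: 11 × 2 = 22.

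More than half are ties, so the median pairwise difference is again 0. The probability of a higher value, counting ties as half, is (174 + 102)/400 = 0.69, which does show the effect. By simulation at 0.15 v 0.45 the shift is 0 in 96% of trials and in 90% of significant ones.

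**7. Limit of a rate ratio.** P(no events in the lower arm) = exp(−0.15 × 20) = exp(−3) = 0.05.

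**The case against.** The strongest reply is that the sparse-count problem may never arise. Only one item is explicitly a count, general practitioner visits, and at plausible frequencies that item hardly ever shows a zero median difference beside a significant test. Admissions and antibiotic use could be recorded as any or none, and would then go to the dichotomous route, where the defect does not exist. The questionnaire is not shown. This stands, and it makes the point conditional. A reader might infer that every non-dichotomous item is a zero-heavy count, including a number of antibiotic courses. The article does not say so: the phrase is "hospital admissions, number of visits to the general practitioner and the use of antibiotics", and the last of these is not described as a number of courses.

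A second reply is that how normality is judged is commonly left to a SAP, and Shapiro-Wilk is only an assumed check. That also stands, so the absence of a criterion is not held against the plan. It does not remove the pairing of Mann-Whitney with "differences in means or differences in medians", which the article fixes itself.

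A third reply is that two thirds is a conditional share. Significant with a zero median difference occurred in 20.5% of all trials at 0.15 v 0.45, and in about 5% at 0.3 v 0.6. That is fair and should be read with the headline figure.

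**Conclusion.** The point holds in a limited form and is minor. The article prescribes an estimate that does not match its test on the non-normal branch. For a sparse item analysed as a count, the estimate is often exactly zero whatever the p-value: about 86% of trials, and about two thirds of significant ones, at assumed Poisson rates of 0.15 v 0.45 with 20 per arm. The share falls quickly as events become more common. For visits averaging 4 v 6 the contradiction is very rare, and what remains is an estimand chosen by the data.

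Two stronger readings are not supported. A reader might infer that choosing the test from the data inflates false positives, but the two-stage error rate stayed close to 5% in the scenarios tried. A reader might also infer that the trial's main result is at risk, but the rule is stated for the 2-year clinical outcomes, while the primary outcome is the day-28 microbiota. The size rests on assumed rates, on admissions or a similar item being recorded as a number, and on the A v B group sizes.

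**What to change.** State for each questionnaire item whether it is recorded as a number or as yes/no, and remove the normality-based switch.

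- **Items recorded as counts:** pre-specify a rate ratio (negative binomial, or Poisson with robust standard errors) or a difference in mean counts, with a 95% CI.
- **If Mann-Whitney is kept:** report the probability of a higher value with its CI. Do not use the difference in medians. Do not use the Hodges-Lehmann shift for sparse counts either, since it is also usually 0 there.
- **Other non-dichotomous items:** name one method in advance.
- **Yes/no items:** leave under the existing dichotomous rule.

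The cost is a few lines of wording and standard software, settled before the 2-year data are analysed. The drawback is that a rate ratio is unstable with very few events and is zero or undefined when an arm has none (about 5% of trials at 0.15 v 0.45). State in advance that the difference in means, or an any/none comparison, is then reported.

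### Student's t-test is prescribed for the unbalanced 40 v 20 caesarean v vaginal comparison of normal 2-year clinical outcomes, so its error rate depends on an unknown SD ratio

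*Protocol article*

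**What the plan says.** The Statistical analysis section of the protocol article sets the test for one class of outcome: "Clinical outcomes at the 2-year follow-up will be compared using Student’s *t*-test or a Mann–Whitney *U* test for continuous variables". The choice between the two tests is made "depending on whether the variables are distributed normally"; no other criterion is given. Differences in means or medians are reported "along with a 95% confidence interval", and the threshold is given as follows: "Differences between study groups will be considered significant if *p* < 0.05".

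The same section lists the contrasts. The first is group A (exposed) against group B (unexposed), the two randomised caesarean groups. Next, "all analyses will compare infants from both CS groups together (groups A and B) with children born vaginally (group C". Last, each caesarean group is set separately against group C.

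The Sample size calculation section gives the planned numbers: "20 born vaginally and 40 born by CS (20 from mothers receiving antibiotics before CS and 20 after clamping of the umbilical cord". It gives no SD or effect size and explains that "A formal power analysis could not be performed as there are currently no relevant data in the literature". The article mentions no unequal-variance test or robust standard error.

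**The concern.** Student's t-test estimates one common variance from both groups. With equal group sizes, unequal spreads largely cancel out of the standard error and the test stays close to its nominal level. At 2:1 they do not cancel. If the smaller group is the more variable, the standard error is too small, so intervals are too narrow and false positives too frequent. If the larger group is the more variable, the standard error is too large and power is lost. This happens with perfectly normal data, so choosing between Student and Mann–Whitney on normality gives no protection.

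Pooling A and B creates exactly this imbalance against C. Nothing in the article supports equal spread: group C is recruited separately, is not randomised and has some exclusion criteria of its own. At stake is whether the stated significance level and 95% coverage hold for the pooled caesarean v vaginal comparison of those 2-year outcomes that reach the t-test.

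**Working it through.** **Inputs.** From the article: n = 40 (A+B) and n = 20 (C); Student's t-test for normal data; threshold 0.05. Assumed: a two-sided test (sidedness is not stated), normal data, equal true means, and an SD ratio r = SD(C)/SD(A+B). The article has no power or SD figure to reproduce; the only nominal figure is 0.05.

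**Formula.** Set SD(A+B) = 1.

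- Variance of the difference that Student's test estimates, on average: V_S = [(39 + 19r²)/58] × (1/40 + 1/20)
- True variance: V = 1/40 + r²/20
- Large-sample two-sided error: 2 × [1 − Φ(1.96 × √(V_S/V))]

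Example, r = 1.25 (r² = 1.5625):

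- V_S = [(39 + 29.69)/58] × 0.075 = 0.0888
- V = 0.025 + 0.0781 = 0.1031
- V_S/V = 0.861, and 1.96 × √0.861 = 1.819
- error = 6.9%

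The formula was checked by simulation, with 1,000,000 trials per ratio.

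| r | V_S/V | Student, formula | Student, simulated | Welch, simulated |
|---|---|---|---|---|
| 0.50 | 1.509 | 1.6% | 1.8% | 5.0% |
| 0.67 | 1.299 | 2.6% | 2.6% | 4.9% |
| 0.80 | 1.161 | 3.5% | 3.5% | 4.9% |
| 1.00 | 1.000 | 5.0% | 5.0% | 5.0% |
| 1.25 | 0.861 | 6.9% | 6.9% | 5.1% |
| 1.50 | 0.769 | 8.6% | 8.5% | 5.0% |
| 2.00 | 0.661 | 11.1% | 11.2% | 5.0% |

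Coverage of the nominal 95% interval is 100% minus the error: about 98% at r = 0.5 and about 89% at r = 2. With losses to 32 v 16 the pattern is the same (1.8% at r = 0.5, 11.4% at r = 2).

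**Balanced contrasts.** At 20 v 20, V_S = V for every r. Simulated Student error is 5.0% to 5.3% for r from 0.5 to 2.

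**Effect of mixing A and B.** Suppose A and B differ in mean by d within-group SDs, all three groups have SD 1, and C's mean lies midway between A and B. The sample variance of A+B absorbs the A–B gap: its expected sum of squares is 39 + 40(d/2)². The mean of a fixed 20 + 20 does not vary with that gap, so the true variance stays at 0.075.

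- d = 1: sum of squares 49. Student: (49 + 19)/58 × 0.075 = 0.0879, ratio 1.172, error 3.4%. Welch: (49/39)/40 + 1/20 = 0.0814, ratio 1.086, error 4.1%.
- d = 2: sum of squares 79. Student: (79 + 19)/58 × 0.075 = 0.1267, ratio 1.690, error 1.1%. Welch: (79/39)/40 + 1/20 = 0.1006, ratio 1.342, error 2.3%.

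Simulation gives 3.4% v 4.1% and 1.1% v 2.4%. Both tests are conservative here, Welch less so.

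**Price of Welch.** With equal SDs and an assumed true difference of 0.78 SD at 40 v 20, power is 80.0% for Student and 79.2% for Welch.

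**The case against.** The strongest case against concerns reach, and most of it stands.

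- **Outcomes.** A reader might infer that every caesarean v vaginal p-value is unreliable, including those for the microbiota. The text does not support that. The sentence naming the t-test covers clinical outcomes at 2 years, and then only normal continuous ones. The primary outcome, the day-28 microbiota in A v B, is not assigned to it. The questionnaire items listed under Study materials and samples are mostly yes/no items or counts. The former go to χ² or Fisher's test, and skewed counts would go to Mann–Whitney. Few outcomes may reach this test.
- **Contrasts.** Only the pooled, non-randomised comparison is affected in the full sample. Confounding may well be a larger threat to that comparison than the form of the variance.
- **Evidence of unequal spread.** It is tempting to say that unequal spread is expected because A+B mixes two treatments. That mechanism makes Student's test conservative, not liberal, and Welch only partly corrects it. Separate recruitment of C gives no direction. Inequality cannot be excluded, but it is not shown.
- **Level of detail.** The test's name may be a generic label, and a SAP could settle the variance form. This carries less weight: the article names the test, makes normality the sole criterion and specifies the pooled contrast. That is a stated rule, not an omission.

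**Conclusion.** The point holds in a narrow form and is minor. For normal continuous 2-year clinical outcomes, the prescribed test does not secure 5% error or 95% coverage in A+B v C. The error is about 3.5% to 6.9% for SD ratios of 0.8 to 1.25, and 1.8% to about 11% for 0.5 to 2. These figures rest on normal data, a two-sided test, the planned group sizes and an assumed range of ratios. The actual departure, and even its direction, cannot be known from the article. The documents do not support extending the criticism to the randomised comparison, to the primary outcome, or to a claim that false positives are inflated.

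**What to change.** In the Statistical analysis section, name Welch's unequal-variance t-test, with its confidence interval, for the comparison of A+B with C. It may be used for the other contrasts too at no material cost. In the full sample they hardly need it, but the planned formula-only and breastfed-only analyses may not stay balanced.

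The change is one word and needs no extra data. It costs under 1 percentage point of power if the variances are equal. It holds error near 5% when within-group spreads differ. It should not be described as exact in every case: if A and B have different means, Welch remains somewhat conservative, though less so than Student.

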### Subjects and study population

The study population consists of three groups. The first two groups include 40 pregnant women visiting the outpatient clinic of the Department of Obstetrics and Gynaecology at VUmc during the last trimester of pregnancy. They must have an uncomplicated pregnancy so far and be scheduled for CS. An uncomplicated pregnancy is defined as a normotensive singleton pregnancy, with a normal-weight foetus without maternal or foetal risk factors, delivered without complications at a gestational age of more than 37 weeks. Twenty women will be treated according to the current NICE guidelines for antibiotic administration during CS (group A). These subjects will receive 1500 mg cefuroxime intravenous 30 min prior to skin incision. The remaining 20 women will be treated according to the former protocol (group B) and will be administered 1500 mg cefuroxime intravenous directly after clamping of the umbilical cord. Allocation to a group will be randomised in permuted blocks of 10 using www.random.org. Allocation to a group will be blinded only for the statistician performing the analysis. The third group will include 20 pregnant women with an uncomplicated pregnancy as described above, admitted for outpatient vaginal delivery in VUmc (group C). Exclusion criteria for this group include antibiotics administration during pregnancy or labour and premature rupture of membranes (Table 1). The women delivering vaginally will be recruited at the same time as the women in the other two groups. The neonates born at ≥37 weeks gestational age from mothers included in one of the three study groups will be included following informed consent from both their parents.

**Table 1 Tab1:** Maternal and neonatal exclusion criteria

Maternal exclusion criteria	
Delivery < 37 weeks gestation	
Aged ≤17 years	
Body mass index ≥ 25	
Antibiotic use during pregnancy	
Antibiotic use during labour (group C)	
Immunosuppressive use within 3 months prior to delivery	
Inflammatory bowel disease	
Coeliac disease	
Rupture of membranes before CS (groups A and B)	
Rupture of membranes > 18 h (group C)	
Diabetes mellitus type I or II	
Gestational diabetes requiring insulin	
History of gastro-intestinal surgery	
Alcohol or tobacco use in second or third trimester	
Use of recreational drugs during pregnancy	
Maternal antibiotic use during first month of neonatal life	
Neonatal exclusion criteria	
Congenital gastro-intestinal anomalies	

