Gastro-intestinal surgery during first month of life	
Antibiotic or immunosuppressive medication use during first month of life	

Standard demographic and obstetric variables will be collected. Other variables, including nutrition of the neonate (breast milk or formula) during the first month of life, birthweight, Apgar scores after 1 and 5 min and presence of meconium-stained amniotic fluid, will be collected. Data on maternal and neonatal medication use during pregnancy and the first month postnatally will be collected, as well as data on maternal weight, neonatal length and maternal diet (vegetarian or non-vegetarian).

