### Limitations

There are also some limitations. Because our study will include patients only from a single tertiary hospital, our results cannot automatically be extrapolated to a more general population. Secondly, only a limited number of children (20 born vaginally and 40 born with CS) will be included. The number of anticipated participants is rather low but will allow us to determine whether there are significant differences in neonatal colonisation, which would hypothetically challenge the safety of the NICE guidelines for infant health. Moreover, we aim to investigate whether there are differences regarding health state, since a disturbance in the composition of the intestinal microbiome may have a key role in the pathogenesis of numerous diseases. We scheduled a follow-up at 2 years; however, often the relevant diseases develop much later in life and we intend to perform a follow-up analysis at the age of 5 years.

Furthermore, the microbiota plays a key role in the function and development of the host immune system [40]. In this study, we will not investigate the effect of the timing of antibiotic administration on this immunisation process.

Hypothetically, infants born without being exposed to cefuroxime during CS could still be exposed to antibiotics through lactation. However, cefuroxime has a relatively short half-life in adults and a low peak concentration in breastmilk [40–42]; thus, we consider the potential effect on the composition of the microbiota due to lactation to be negligible. Furthermore, if differences exist between the groups in terms of feeding strategies, we will adjust for this in the statistical analysis.

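### Adjustment of the randomised A v B comparison is triggered by observed imbalance and relies on post-allocation feeding; the covariates should be fixed in advance

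*Protocol article*

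**What the plan says.** The primary outcome is the day-28 difference in microbiota between the two caesarean groups. The planned numbers are "20 born vaginally and 40 born by CS (20 from mothers receiving antibiotics before CS and 20 after clamping of the umbilical cord"). On randomisation, the article states: "Allocation to a group will be randomised in permuted blocks of 10 using www.random.org". It mentions no stratification factor.

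Four statements bear on adjustment:

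- Statistical analysis, opening: "Baseline characteristics will be summarised for all subjects by treatment regimen and compared between groups".
- Statistical analysis, last paragraph: "If differences exist between the groups in terms of feeding strategies or other baseline characteristics, we will adjust for this in the statistical analysis".
- The sentence after that, on nutrition: "we will perform the same analysis for infants fed only by formula and for infants breastfed only and adjust for this factor".
- Limitations: "if differences exist between the groups in terms of feeding strategies, we will adjust for this in the statistical analysis".

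The Subjects and study population section gives the timing of the feeding variable: "nutrition of the neonate (breast milk or formula) during the first month of life".

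**The concern.** Groups A and B are randomised, so any imbalance between them in a true baseline variable is due to chance. A rule that adjusts only for variables found to differ selects on that chance. It can bring in variables unrelated to the microbiota and leave out strong predictors that happen to look balanced. The final model is then unknown until the data are seen.

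Feeding raises a separate problem. It is grouped with baseline characteristics but observed after the mother has been allocated and dosed. If timing of the antibiotic had any effect on feeding, adjusting for feeding would remove part of the effect of the arm, and the A v B estimate would answer a different question.

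The stakes are precision and credibility. With 20 infants per arm, little precision can be spared. The article names the randomised design as its main strength, and a model chosen from the data weakens that.

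**Working it through.** **1. The feeding statements side by side.** The conditional rule appears in Statistical analysis and again in Limitations. Between them stands a promise of formula-only and breastfed-only analyses plus adjustment, with no imbalance condition. Both cannot govern the same analysis. If feeding is adjusted for in any case, the condition is empty. If the condition governs, the unconditional promise is wrong.

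**2. How often chance alone would trigger adjustment.** With k independent baseline variables each tested at 0.05 (the trigger and k are assumptions), the chance that at least one differs is 1 − 0.95^k:

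- k = 5: 1 − 0.774 = 23%
- k = 10: 1 − 0.599 = 40%
- k = 15: 1 − 0.463 = 54%

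**3. Power of the rule.** The article states no power figure, so there is none to reproduce. Inputs from the article: 20 v 20 and significance at p<0.05 (taken as two-sided). Assumed: a continuous outcome such as the Shannon index with SD 1, an effect of 0.8 SD, one prognostic covariate explaining a share R² of the variance, 0, 4 or 9 further unrelated candidates, and adjustment for every candidate that differs at p<0.05. Each row has 20,000 simulated trials; the simulation error of each figure is about √(0.7 × 0.3 / 20,000) = 0.003.

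| R² | Unrelated candidates | Unadjusted | Imbalance rule | Always adjust for the prognostic covariate |
|---|---|---|---|---|
| 0.15 | 0 | 0.698 | 0.700 | 0.755 |
| 0.15 | 4 | 0.696 | 0.682 | 0.750 |
| 0.15 | 9 | 0.692 | 0.665 | 0.751 |
| 0.25 | 0 | 0.697 | 0.705 | 0.803 |
| 0.25 | 4 | 0.694 | 0.688 | 0.800 |
| 0.25 | 9 | 0.692 | 0.672 | 0.803 |
| 0.40 | 0 | 0.693 | 0.705 | 0.879 |
| 0.40 | 4 | 0.689 | 0.691 | 0.879 |
| 0.40 | 9 | 0.694 | 0.677 | 0.882 |

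Against fixed adjustment the rule loses in every row, from 0.755 − 0.700 = 5.5 points to 0.882 − 0.677 = 20.5 points. Against no adjustment it ranges from 0.705 − 0.693 = 1.2 points better to 0.692 − 0.665 = 2.7 points worse.

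**4. Sensitivity to the trigger.** With one candidate, R² = 0.25 (correlation 0.5) and an effect of 0.9 SD, power is 0.793 unadjusted and 0.885 with fixed adjustment. The rule gives 0.801 (p<0.05), 0.807 (p<0.10), 0.817 (p<0.20), 0.841 (standardised difference above 0.25) and 0.867 (above 0.1). A looser trigger narrows the loss, from 0.885 − 0.801 = 8.4 points to 0.885 − 0.867 = 1.8 points, but does not remove it.

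**5. Type I error.** With one candidate and correlation 0.5, it is 0.049 unadjusted, 0.050 with fixed adjustment and 0.043 under the p<0.05 rule. The rule is slightly conservative, not inflated.

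**6. Feeding as a post-allocation variable.** Assume a direct effect of arm of 0.5 SD, a feeding effect of 1 SD, and breastfeeding of 50% in one arm and 70% in the other because of the arm. The total effect is 0.5 + (0.50 − 0.70) × 1 = 0.30 SD. In simulation the adjusted analysis estimates 0.50 and the imbalance rule averages 0.40, which is neither quantity. When the arm does not affect feeding (60% in both), all three analyses are centred on 0.50 and there is no bias.

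**The case against.** **A reader might infer that the rule has less power than no adjustment at all.** The working does not support that as a general statement. It happens when several unrelated variables are screened at p<0.05, and it reverses with a single candidate. The article fixes neither the number of candidates nor the trigger.

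**A reader might also infer that a feeding imbalance short of significance would go unadjusted and bias the result.** The unconditional sentence on formula-only and breastfed-only analyses stands against that. A chance imbalance in one trial is in any case not a bias of the randomised estimator.

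**Scope.** The rule speaks of the groups in general, and the section also plans comparisons with the vaginally born group C. There, differences are not mere chance and adjustment is warranted. This stands, and the point is limited to A v B. Apgar scores and neonatal medication are listed as data to be collected but are never called baseline, so only feeding is mislabelled.

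**Mechanism.** Both arms receive the same drug and dose at different times, and the article gives no reason why timing should alter feeding. This also stands: the change in what is estimated is conditional, not demonstrated.

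**Blinding and an unseen SAP.** The analysing statistician is blinded to allocation, which limits steering the model towards one arm. It does not stop the data from choosing the model. A covariate list may sit in an SAP that is not shown, and its absence from the article is not the complaint. The complaint is the rule that the article does state.

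**Size of the gain.** Nothing in the article shows that any pre-delivery covariate explains 15% to 40% of the variance. This stands too.

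**Conclusion.** The point holds for the randomised comparison. The stated rule lets observed imbalance choose the model, places a post-allocation variable among baseline characteristics, and conflicts with the unconditional feeding analyses promised in the next sentence.

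For a 0.8 SD effect and a p<0.05 trigger, the cost relative to pre-specified adjustment is about 5 to 21 power points. It depends on how prognostic the covariate is and how many candidates are screened. The effect size, R², trigger and number of candidates are all assumptions. Type I error is not inflated in these settings, and power is roughly that of an unadjusted test. The fault is therefore lost precision and an open model rather than a false-positive risk shown by the calculation. The feeding problem changes the estimate only if the arm affects feeding.

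**What to change.** In the Statistical analysis section, and in any SAP that follows it:

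1. Delete the imbalance trigger for A v B, here and in Limitations.
2. Name two or three covariates that are known before delivery, already collected and expected to be prognostic, and adjust for them whatever the observed balance. Maternal diet is listed as collected, and gestational age would fall under the standard obstetric variables, although restriction to term births may limit its value. Planned feeding is not listed, so it could be used only if recorded.
3. Tabulate baseline characteristics by group without significance tests.
4. Reconcile the two feeding sentences: keep the A v B analyses stratified by or adjusted for observed first-month feeding, labelled as sensitivity analyses.
5. For comparisons with group C, keep confounder adjustment, which may include feeding, but fix the set in advance.

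The cost is a change of wording and two or three degrees of freedom. The gain is only as large as the chosen covariates are prognostic.
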